#### Aim 3: To evaluate the relative influence of gender networks on LPG adoption in rural households

We will use personal network data of males and females in both the adopter and non-adopter groups from our sample of households. We will analyze network structure and composition characteristics. For structure, we will explore structural holes (constraint, effective size and efficiency) of social networks across the case and control groups [41]. We will also assess the network density, which describes the number of actual connections compared to the number of potential connections in the network [39, 42]. For composition analysis, we will assess the proportion kin in the networks, and variation across other characteristics (age, cooking habits). We will test the hypothesis that men tend to initiate information and disseminate them to longer distances on issues of cleaner stoves adoption [39]. However, we will also be able to examine if the gender balance shifts and women dominate men in information exchange at closer distances.

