
The RE-AIM framework emphasizes multilevel and concurrent examination of household and organizational level factors driving adoption, implementation, and maintenance of health interventions, instead of an isolated examination of such levels [33, 34, 36]. It seeks to address the ‘voltage drop’ as interventions move from efficacy testing to real world sustainment [37]. The barriers and enablers of adoption and use occur at individual and possibly at organizational levels. The study protocol allows us to examine both these levels [34]. Similarly, individual and organizational level factors may influence effectiveness of an intervention [34, 36]. While affordability is a household level factor, accessibility and awareness of LPG cut across household and organizational level factors. RE-AIM framework allows us to examine how affordability, accessibility, and awareness at multiple levels influence adoption and sustained use of LPG [33, 34, 36] in study aim 1 and study aim 2. In addition, gender networks in communities also influence uptake and use of health interventions [38]. Aim 3 explores the relative influence of personal gender networks of males and females in selected households and their impact on LPG adoption. Figure 2 synthesizes the placement of the three aims and analyses of our study within the RE-AIM framework.

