### Study participants (*N* = 510; 255 from each group)

The inclusion criteria for the study participants are: rural household with an adult male and female member (>18 years age), woman respondent who is able to provide consent for the study, the woman respondent is the primary cook of the house, senior most male respondent (or primary male decision maker in the household) who is able to provide consent for the study, women respondent residing in the household for the last 12 months, women respondent plans to reside in the household for at least 12 months from the date of enrollment for the study. An additional inclusion criterion for case group (LPG adopter households) is: household has received the first LPG cylinder in the last 12 months from the date of enrollment for the study.

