#### Aim 3: To evaluate the relative influence of gender networks on LPG adoption in rural households

Personal social networks of individuals in communities influence awareness levels, which in turn drive adoption, implementation, and maintenance of stoves [39]. Implementation of health interventions are impacted by the personal networks of men and women in the households [38, 39]. Both men and women play a critical role in adopting, implementing, and maintaining cleaner cooking technologies like LPG [39]. Thus, it is critical to assess the personal networks of study participants to ascertain how they influence (or get influenced by) decisions related to making a fuel switch. To generate personal network data, we will use a personal network survey to probe the women (primary cook) and the adult male (or primary male decision maker) of 100 households each in the case and control groups. This approach is novel in understanding the role of gender dimensions and the peer effects impacting their fuel choice. Personal social networks, or egocentric networks, focus on the structure and composition of the networks surrounding a target individual [40]. We will use a well-established ego-centric network survey instrument to measure personal networks of men and women. The gendered network data will be collected as follows: 1) the survey will begin with three name generator questions to prompt identification of individuals who give advice, socialize, and support the respondent. 2) After eliciting the network members, a second set of questions will be performed to evaluate the strength of the connections (tie strength) between the respondent and the individuals identified by the respondent; 3) subsequently, the strength of the connections between the network members identified will be probed; 4) finally, characteristics of the network members identified will be solicited (e.g., their demographics, income, household size, and cooking habits).

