### Research instruments

A summary of the research instruments is provided in Table 2. Each of the research instruments will be drafted in English and will be translated into Telugu (local language of the region in India).

**Table 2 Tab2:** Data collection instruments

Conceptual domains	Aims	Research instrument	Method or Measure	Data source	Sample size
Adoption of LPG	Aim 1	Adoption questionnaire	Structured interview	Households: women	LPG adopter households (case): 255; Non-LPG adopter households (control): 255
Sustained use of LPG	Aim 2	SUMS	Stove temperature monitoring	Households: LPG and traditional stoves	LPG adopter households (case): 100
Sustained use of LPG	Aim 2	Follow up questionnaire	Structured interview	Households: women	LPG adopter households (case): 100
Personal social networks of LPG adopters and non-LPG adopters impacting adoption of LPG	Aim 3	Social network survey questionnaires for women and men	Structured interview	Households: women, men	LPG adopter households (case): 100 Non-LPG adopter households (control): 100

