### Limitations

There are limitations of this study. Each of these limitations is briefly considered below.
**Study design:** The retrospective nature of aim 1 and aim 3 in the study for LPG adopters might lead to concerns of recall bias, which may limit the accuracy of participants’ memories on factors of 3As, which impacts adoption. However, engaging a large sample size of 510 households in such geographically proximal households might reduce the issues of recall bias [43]. Similarly, the retrospective nature of data from follow-up questionnaire for aim 2 might also be subject to recall bias.
**Data analyses:** Regression of sustained use (SUMS data) on its determinants (3As) (from follow up questionnaires) will be done for a small sample size of 100 households. Smaller sample size might preclude us from conducting multilevel analyses by controlling for institutional level predictors.
**Exploratory study:** There is limited empirical evidence available on the impact of 3As on adoption and sustained use of LPG. This study is primarily exploratory and developmental in nature. However, it is expected that this study will inform future research to develop and test the effectiveness of implementation strategies for LPG adoption and use in resource poor settings within the RE-AIM framework. In addition, findings from the study will provide insights on the estimate of effect size to facilitate a larger R01 study on the impact of 3As on LPG adoption and sustained use in such communities.

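### Aim 3 surveys adopters' networks after uptake and, as described, does not date contacts' LPG use, so contacts who followed the household cannot be told from contacts who influenced it

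*Protocol article*

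**What the plan says.** The target is directional. The section on the RE-AIM evaluation framework describes aim 3 as the relative influence of "personal gender networks of males and females in selected households and their impact on LPG adoption". The aim 3 data collection section speaks of the "role of gender dimensions and the peer effects impacting their fuel choice". The same section accepts that influence may run either way: networks are assessed to "ascertain how they influence (or get influenced by) decisions related to making a fuel switch".

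On measurement, the survey elicits contacts through name generators and then tie strength. Finally, "characteristics of the network members identified will be solicited (e.g., their demographics, income, household size, and cooking habits") are recorded. No reference time is given for any of these items.

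On analysis, the aim 3 section lists structural holes, density and composition. For composition, "we will assess the proportion kin in the networks, and variation across other characteristics (age, cooking habits"). It also states a hypothesis about men and women passing on information at longer and shorter distances.

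On timing, the additional criterion for cases under Study participants is: "household has received the first LPG cylinder in the last 12 months from the date of enrollment for the study". The sample in Table 2 is "LPG adopter households (case): 100 Non-LPG adopter households (control): 100". Under Limitations the only related remark is: "The retrospective nature of aim 1 and aim 3 in the study for LPG adopters might lead to concerns of recall bias".

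**The concern.** In a case-control comparison, an exposure counts as a candidate cause of the outcome only if it came before the outcome. Here the outcome is the household's uptake of LPG, and the most direct peer exposure is the presence of contacts who already cook with LPG. Every case household has taken up LPG before its network is surveyed. Unless contacts' habits are dated, the case networks include any friends or relatives who switched after seeing the household do so. Those contacts raise the measured exposure among cases, although they are a result of adoption.

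The article names both directions of influence and then describes no item or analysis step that separates them. Recall bias is a different problem: perfectly accurate answers about contacts' present habits would still mix leaders with followers. At stake is the main inference of aim 3, which could credit networks with an effect that the adopting household had on them. A date that is not collected in the field cannot be recovered at analysis.

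**Working it through.** **Order of events.** Four statements in the article, set side by side:

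1. Cases have had their first cylinder by enrolment (Study participants).
2. The survey records contacts' cooking habits, with no time anchor described (Data collection, aim 3).
3. The analysis compares networks of adopters and non-adopters, with no before/after step (Data analysis, aim 3).
4. The conclusion sought is the networks' effect on adoption (RE-AIM evaluation framework; Data collection, aim 3).

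Statements 1 to 3 do not identify the direction that statement 4 needs. The household's side of the dating is nearly in hand, because the aim 1 questionnaire records months of LPG ownership in cases. Only the contact's side is missing.

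**Possible size.** The article gives no figure for this point. Its one power calculation concerns income: 2 × (1.960 + 0.842)² × (2199.26/545.35)² ≈ 255 per group. That reproduces but has no bearing here. The illustration below takes only 100 v 100 networks (Table 2) and two-sided alpha 0.05 (Sampling and recruitment) from the article. Everything else is assumed:

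- k = 5 or 8 contacts per network, independent of each other;
- q = 20% or 40% of contacts on LPG irrespective of the household;
- no influence of contacts on the household;
- a fraction r of non-LPG contacts follows the household, in case networks only.

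The expected LPG share is q in control networks and q + (1 − q)r in case networks.

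Worked case, k = 5, q = 0.20, r = 0.05:

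- case share = 0.20 + 0.80 × 0.05 = 0.24; difference = 0.04
- standard error = √[(0.24 × 0.76 + 0.20 × 0.80)/(5 × 100)] = √(0.3424/500) = 0.0262
- ratio = 0.04/0.0262 = 1.53; chance of a significant result ≈ Φ(1.53 − 1.96) = 0.33

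Simulation (20,000 repeats, Welch test of mean LPG share) agrees:

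| Contacts | Control share | Case share, 5% follow | Falsely significant | Case share, 10% follow | Falsely significant |
|---|---|---|---|---|---|
| 5 | 20% | 24% | 33% | 28% | 84% |
| 5 | 40% | 43% | 16% | 46% | 48% |
| 8 | 20% | 24% | 49% | 28% | 96% |
| 8 | 40% | 43% | 23% | 46% | 67% |

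With r = 0 the rate is about 5%. Counting only contacts who used LPG before the reference date reproduces that case, if they are dated correctly.

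**Sensitivity.**

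- If control networks show half of the follow-on uptake, the rates fall to 8% to 16% (5% follow) and 16% to 44% (10% follow).
- With a within-network correlation of 0.2 instead, they are 11% to 25% and 31% to 72%.
- If the summary were the heterogeneity p(1 − p) rather than the share, they are about 7% to 43% and 11% to 93%. The timing problem therefore does not depend on which of the two is used.

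**The term variation.** If it means a within-network index of a yes/no LPG item, p(1 − p) gives 0.2 × 0.8 = 0.16 at a 20% share and 0.8 × 0.2 = 0.16 at 80%. Such an index does not show which way exposure points. For a true 60% v 40% difference, the share detects it in over 99% of simulated studies and the index in about 5%. For 20% v 30%, the index still detects it in about 87% to 98%. The loss is severe only when the two shares lie symmetrically about 50%.

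**The case against.** The strongest reply is that this is a condensed article. It cites an established egocentric instrument that is not shown, introduces the contact characteristics as examples, and calls aim 3 retrospective. The instrument may well ask about the past. A reader might infer that habits are recorded as at interview; the text does not say so. What stands against this reply is that the article describes the data and the analysis in some detail, acknowledges both directions of influence, and offers no means of separating them.

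A reader might also infer that the summary makes an all-LPG network look like an all-biomass one. That follows only if variation means a within-network heterogeneity index of a yes/no item. The phrase may equally mean how habits differ between the case and control groups, and the article speaks of cooking habits, not of LPG yes or no. Where 20% to 40% of contacts use LPG, even the index would mostly work. This reading is not supported as a defect; what remains is an unclear term.

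Third, cooking habits are not the only route to a network effect. Tie strength, structural holes, density, kinship and the information-flow hypothesis are also planned, and the study calls itself primarily exploratory. That limits how much of aim 3 is affected. It does not remove the problem where peers' fuel use is taken as an influence on adoption.

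Finally, cases and controls come from the same habitations, so their networks may overlap and follow-on uptake may appear in both. This is fair, and the sensitivity figures show that it lowers the rates considerably.

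**Conclusion.** The point holds in a limited form. As described, aim 3 does not place contacts' cooking habits before the case household's own uptake, so it cannot separate influence on the household from influence by it. The limitations section does not acknowledge this. The conclusion rests on the order of events stated in the article and on the absence of any described item or step that resolves it; an unseen instrument could already do so.

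The size is illustrative only. With no true peer effect, the false-difference rate for the LPG share is about 16% to 49% if 5% of non-LPG contacts follow the household and 48% to 96% if 10% follow, against about 5% if none do. Network size, LPG share, switching rate, independence of contacts and switching confined to case networks are all assumptions. The figures are not error rates of the plan itself, and they fall if control networks share the uptake.

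**What to change.** For each contact who cooks with LPG, ask whether that use began before or after the household's first cylinder. For control households, take as reference the first-cylinder date of an enrolled case in the same habitation. The design selects equal numbers of cases and controls in each habitation, so such a date is available. Giving controls a reference date matters: otherwise their contacts would be counted up to the interview and those of cases only up to uptake.

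State as the composition measure of peer exposure the proportion of contacts already using LPG at the reference date, compared between cases and controls separately for the man's and the woman's network. Keep variation in cooking habits as a secondary description and say what it means. Add reverse direction to the limitations beside recall bias. If the existing instrument already dates contacts' uptake, saying so and naming the proportion is enough.

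The cost is one extra question per LPG-using contact, a changed summary, and some recall error in the before/after answer. The change fixes the order in time only. Contacts are still named at interview, and factors shared by a household and its contacts can still produce an association. It has to be made before fieldwork.

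### As described, neither the network survey nor the planned measures capture who starts or passes on stove information, which aim 3's only stated hypothesis needs; its distance term is undefined

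*Protocol article*

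**What the plan says.** Under Data analysis, Aim 3, the protocol article states a directional hypothesis about men and women: "We will test the hypothesis that men tend to initiate information and disseminate them to longer distances on issues of cleaner stoves adoption". It adds a companion contrast, that the study can "examine if the gender balance shifts and women dominate men in information exchange at closer distances".

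Under Data collection, Aim 3, it describes the data. The design is egocentric; such networks "focus on the structure and composition of the networks surrounding a target individual". The survey has four numbered blocks:

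1. "three name generator questions to prompt identification of individuals who give advice, socialize, and support the respondent"
2. questions to "evaluate the strength of the connections (tie strength) between the respondent and the individuals identified by the respondent"
3. "the strength of the connections between the network members identified will be probed"
4. "characteristics of the network members identified will be solicited (e.g., their demographics, income, household size, and cooking habits", an open list of examples.

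For the analysis, the structural part is "we will explore structural holes (constraint, effective size and efficiency) of social networks across the case and control groups", plus network density. The compositional part is the share of kin and the variation in age and cooking habits. The woman and the man are interviewed in 100 adopter and 100 non-adopter households.

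**The concern.** The hypothesis is about a process: a man or a woman raises the subject of cleaner stoves and the information travels some distance. The survey and measures, as described, give the shape and make-up of each person's circle. Shape and make-up do not show who spoke first, about what, or whether anything was passed on.

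This is not just detail left out of a condensed article. The article sets out the survey content and the measures, then announces a test that they do not serve. If the study runs that way, the test may be dropped without comment. Alternatively, a male-female difference in density or constraint may be reported as evidence on who spreads stove information. The article presents the gendered network analysis as a main novelty of the study, so such a reading would carry weight.

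**Working it through.** No calculation applies: the plan gives no figure for this hypothesis. The check sets what the hypothesis needs against what is described.

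**What the hypothesis needs, per tie**

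- (a) that stove or LPG information was exchanged;
- (b) who raised it;
- (c) that the respondent passed it on;
- (d) a distance, under some definition.

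**The four survey blocks (Data collection, Aim 3)**

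| Block | (a) topic | (b) who raised it | (c) passed on | (d) distance |
|---|---|---|---|---|
| Name generators | no, general | no | no; advice and support run towards the respondent, socialising has no direction | no |
| Respondent-contact tie strength | no | no | no | only if distance means social closeness |
| Contact-contact tie strength | no | no | no; shows a possible path, not that anything travelled along it | no |
| Contact characteristics | no; cooking habits show what the contact does, not what was discussed | no | no | residence is not named, but the list is open |

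Items (a), (b) and (c) are therefore met in 0 of 4 blocks.

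**The listed measures (Data analysis, Aim 3)**

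The count is constraint, effective size and efficiency (3), density (1), share of kin (1), age and cooking habits (2): 3 + 1 + 1 + 2 = 7. None of the 7 carries (a), (b) or (c). Share of kin could bear on (d) if distance is read as social.

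**Three readings of distance**

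- *Geographic.* The only distances the article describes run from habitations or households to the LPG distribution center (Sampling and recruitment; Data collection and Data analysis, Aim 1). Distance from respondent to contact is not named.
- *Network steps.* An egocentric survey sees the respondent, the named contacts and the ties among them. Spread beyond those contacts is not observed.
- *Social.* Tie strength is collected on every respondent-contact tie, and share of kin is to be analysed. Either could serve, but the article does not say so.

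**Sample.** 100 + 100 = 200 households, with two respondents each, gives 200 × 2 = 400 interviews.

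**The case against.** The strongest reply is that the article summarizes an instrument it does not show. It gives about one sentence per block, cites an established egocentric instrument, and introduces the contact characteristics as examples only. The list is visibly incomplete: kinship is not named in it, yet the share of kin is to be analysed. A residence item could exist in the same way, perhaps under demographics. This stands, and it is why the point on distance is limited to a missing definition. A reader might infer that distance is not measured at all; the document does not support that.

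Second, direction is not wholly absent, because asking who gives advice records something inbound. That is true but of little help. The question is not about stoves, and it records what the respondent receives, whereas the hypothesis concerns what the respondent starts and spreads.

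Third, the limitations section calls the study mainly exploratory, and the core of aim 3 is the comparison of networks between adopters and non-adopters. This limits the consequence. It does not remove the mismatch, because the text still says the hypothesis will be tested.

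The open list of contact characteristics does not easily cover initiation. Who raised stoves in a given exchange is a property of the tie, not of the contact, and the two tie blocks are described as strength only.

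**Conclusion.** The point holds for the survey and measures as described. Initiation, stove-specific exchange and onward passing appear in none of the four blocks and none of the seven measures. This is the firm part. Distance is undefined and its geographic form is not among the named items; this part is less certain. The conclusion assumes that the unseen questionnaire follows the published outline.

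The effect is confined to aim 3's one stated hypothesis and its companion contrast on closer distances. It should be put right before fielding, because who raised a subject is hard to recover afterwards.

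Two stronger readings are not supported:

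- That the 400 interviews would be wasted. They still serve the comparison of structure and composition across the two groups.
- That contacts' cooking habits are recorded as of the interview, so that a contact who copied the respondent is bound to look like an influence on the respondent. The article gives no reference time for that item, and it acknowledges that influence may run either way. Timing is a separate matter, for which an optional item is given below.

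**What to change.** Take one of two routes before fielding.

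**Route 1: measure what the hypothesis needs.** For each named contact, ask whether LPG or stoves were discussed, who raised it first, and the contact's village or approximate distance. State which meaning of distance is intended. Test the hypothesis at tie level: exchange initiated by the respondent as the outcome, with respondent sex, distance and their interaction as predictors, allowing for ties clustered in respondent and household. Confine the claim to exchanges with named contacts, since spread beyond them stays unobserved.

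**Route 2: reword the hypothesis** to a male-female comparison of structure and composition that the planned measures can answer. This adds no interview time, but it gives up the statement about who starts and spreads information.

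**Optional.** Ask adopters whether the contact had LPG before the respondent's first cylinder, so that influence on the respondent can be told apart from influence by the respondent. Controls are balanced with cases in number within each habitation, not individually matched, so they have no reference date; one would have to be assigned.

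**Cost.** Route 1 lengthens the interview somewhat. With m contacts named, three items add up to 3 × m questions per respondent. The article does not give m, so the added time cannot be stated.
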